## Introduction

### Background

Autism spectrum disorder (ASD) is a lifelong neurodevelopmental condition characterized by persistent differences in social communication and interaction, alongside restricted and repetitive patterns of behavior and interests [1]. Beyond these core diagnostic features, many autistic individuals experience clinically meaningful motor impairments, including reduced coordination, poor balance, atypical gait, and diminished muscle strength [2-5]. These impairments often persist into adulthood and across the life course [6-9], yet they remain relatively underrecognized in adult ASD research and clinical care. Motor limitations may reduce participation in physical activity (PA), increase sedentary behavior, and contribute to an elevated risk of falls, obesity, and chronic health conditions, ultimately affecting overall functioning and quality of life (QoL).

Despite their relevance, motor impairments and physical function remain underresearched in adults with ASD. These domains are not included in diagnostic criteria, are inconsistently assessed in clinical practice, and are infrequently addressed through movement-based rehabilitation strategies [2,10,11]. The limited use of standardized, objective measures of physical function in autistic adults also restricts the ability to evaluate intervention effects, monitor change over time, and tailor supports to individual needs [10]. This gap underscores a pressing need for accessible, valid, and reliable methods to assess physical function and motor performance in adults with ASD.

Barriers to health care access further complicate the evaluation and management of physical function in this population. Adults with ASD often encounter communication challenges, sensory sensitivities, anxiety, and limited provider familiarity with adult ASD, all of which may interfere with effective assessment and treatment [12-14]. These barriers are often compounded for racial and ethnic minority populations, who may also experience delayed diagnosis, underrecognition of co-occurring conditions, and structural inequities in care [15-17]. Additional barriers related to transportation, geography, financial constraints, and health system complexity may further reduce participation in clinic-based care [18-20]. Telehealth-based approaches may help address these barriers by reducing logistical burdens, minimizing sensory and social stressors, and expanding participation in both research and clinical services.

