	Co-Morbidity Index [46]	Impact of chronic health conditions on functional outcomes		Personal factors	
	GSLT-PAQ^l^ [47]	Self-reported leisure-time physical activity participation		Activities/participation	
	Demographics: age, race, ethnicity, sex, city, state, ZIP code	Age, race, ethnicity, gender, and geographic characteristics (city, state, and ZIP code)		Personal/environmental factors	
SPARK^m^ registration data					
	Social Responsiveness Scale-Autism Severity [48]	Quantitative measure of social impairment associated with ASD^n^ relatively stable trait over time		Body functions activities and participation	

^a^ICF: International Classification of Functioning, Disability, and Health.

^b^5xSTS: Five Times Sit-to-Stand.

^c^30sSTS: 30-Second Sit-to-Stand.

^d^BBS: Berg Balance Scale.

^e^SLS-R/L: right/left single-leg stance.

^f^STEADI: Stopping Elderly Accidents, Deaths, and Injuries.

^g^LEFS: Lower Extremity Functional Scale

^h^PROMIS: Patient-Reported Outcomes Measurement Information System.

^i^PF: physical function.

^j^QoL: quality of life.

^k^IS: instrumental support.

^l^GSLT-PAQ: Godin-Shephard Leisure-Time Physical Activity Questionnaire.

^m^SPARK: Simons Powering Autism Research and Knowledge.

^n^ASD: autism spectrum disorder.

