#### PROMIS-Global Health

The PROMIS Global Health measure includes 10 items that assess key domains of overall health and well-being [55]. These domains include general health, physical function, pain, fatigue, emotional distress, and social satisfaction. The measure yields 2 summary scores: Global Physical Health (GPH) and Global Mental Health (GMH), both standardized as T-scores based on the US general population. This brief, validated tool is well-suited for remote administration and provides a comprehensive snapshot of participants’ self-reported health status.

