#### PROMIS-Instrumental Support

PROMIS-Instrumental Support (PROMIS-IS) will be used to assess perceived social support and interpersonal relationships. The PROMIS measures are scored using T-scores for comparison with the large sample mean corresponding to the development of these measures, with higher scores indicating greater satisfaction or fewer limitations [45].

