### Statistical Data Analysis Plan

All analyses will be conducted using 2-sided tests with a significance level of α=.05. Descriptive statistics will summarize participant characteristics and study variables. Continuous variables will be summarized using means and standard deviations or medians and interquartile ranges, as appropriate, and categorical variables using frequencies and percentages. Prior to inferential analyses, assumptions of normality, linearity, homoscedasticity, and absence of multicollinearity will be evaluated. If the assumptions for parametric analyses are not met, appropriate nonparametric or robust analytic methods will be applied.

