An a priori power analysis was conducted using G*Power (version 3.1.9.7; Heinrich Heine University Düsseldorf) [63]. Assuming a 2-tailed α=.05 and power=0.80, a total sample size of N=155 provides adequate power to detect small-to-moderate correlations (r ≥ 0.25-0.30), consistent with expected construct validity effect sizes. PROMIS-PF scores are expected to demonstrate moderate positive correlations with habitual PA and performance-based functional measures and moderate-to-strong positive correlations with other self-reported function scales. Negative correlations are anticipated with fall risk indicators and comorbidity burden. In addition to the power-based justification, precision was considered. At N=155, correlation estimates are expected to have reasonably narrow 95% CIs, supporting adequate precision in estimating associations [64].

The sample size for reliability analyses was informed by Borg et al [59]. Assuming 2 repeated measurements per rater, a subsample of n=25 is expected to provide sufficient precision to estimate ICC values ≥0.75, consistent with recommendations for reliability studies.

The full sample (N=155) will be used for primary construct validity analyses, while the nested subset (n=25) will support exploratory performance-based validity analyses and reliability estimation.

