#### Aim 2: Racial and Ethnic Disparities in Physical Function, PA, and QoL

To examine racial and ethnic disparities in physical function, PA, personal and environmental factors, and QoL among adults with ASD, analysis of covariance models will be used to compare adjusted mean outcomes between non-Hispanic White participants and participants from racial and ethnic minoritized groups. Covariates such as sex and autism severity will be included as appropriate to reduce confounding. If analyses are expanded to include more than 2 racial and ethnic groups, omnibus models will first be conducted, followed by multiplicity-adjusted pairwise comparisons where the overall test is statistically significant. Effect sizes and 95% CIs will be reported alongside *P* values. The planned sample size of 155 participants is expected to provide adequate power to detect medium-sized effects and to generate preliminary disparity estimates for future studies [63].

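### Aim 2 names autism severity as a covariate against confounding but states no group contrast without it; the two contrasts should be reported side by side

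*Protocol article*

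**What the plan says.** The Aim 2 section of the statistical plan compares ANCOVA-adjusted means between non-Hispanic White participants and participants from minoritized groups. The outcomes are physical function, physical activity, personal and environmental factors, and quality of life. On covariates it says: "Covariates such as sex and autism severity will be included as appropriate to reduce confounding". It mentions no unadjusted or demographics-only comparison. The Objectives section presents the aim as preliminary evidence on how health and functioning differ between groups.

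Severity is the SRS score taken from the registry. Table 1 describes it as "Quantitative measure of social impairment associated with ASD" and also as a trait that changes little over time. The SRS section adds that scores show some temporal variability and that the administration date is unavailable.

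Two outcome instruments have social content. Of PROMIS-Global Health, which Table 1 uses for quality of life, the article says: "These domains include general health, physical function, pain, fatigue, emotional distress, and social satisfaction". PROMIS-Instrumental Support, the environmental-factor measure, "will be used to assess perceived social support and interpersonal relationships". The Background describes racial and ethnic minority populations as groups "who may also experience delayed diagnosis, underrecognition of co-occurring conditions, and structural inequities in care".

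**The concern.** Aim 2 asks how large the group differences are. In the usual sense, a confounder of a group difference is a common cause of group membership and outcome. Autism severity is not a cause of race or ethnicity, so the stated reason for adjusting does not fit it well. Two other roles are possible:

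- **Case-mix or selection.** If recognition and registration differ by group, severity among registrants can differ for that reason. Adjustment is then informative.
- **Pathway or overlap.** If unequal access affects social functioning, or if the SRS and the outcome partly measure the same thing, adjustment removes part of the difference that Aim 2 sets out to describe.

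In either case, the SRS-adjusted contrast answers a narrower question: what difference remains among people of equal measured severity? If it stood alone under the name of disparity, a reader could not tell how far it departs from the overall difference, or in which direction. Aim 2 is meant to supply preliminary estimates for later studies, so the ambiguity would carry forward.

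**Working it through.** **1. The plan's own figure.** The power statement under Aim 1 claims that N=155 is adequate for correlations of 0.25 to 0.30 (two-sided α=.05, power 0.80). With N = ((z₀.₉₇₅ + z₀.₈₀)/atanh(r))² + 3:

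- r = 0.25: N = 124
- r = 0.30: N = 85

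N=155 gives power 0.88 and 0.97, so the claim holds. The present point does not depend on it.

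**2. Scale for Aim 2.** The section says "The planned sample size of 155 participants is expected to provide adequate power to detect medium-sized effects" and gives no number. I take medium as 0.5 SD; this is an assumption.

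**3. Where the content overlaps.**

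| Aim 2 measure | Content according to the article | Overlap with a social-impairment score |
|---|---|---|
| PROMIS-Global Health (QoL) | includes social satisfaction | yes, in part |
| PROMIS-Instrumental Support | social support, relationships | yes |
| PROMIS-PF | ability to do physical activities | weak: only a shared ICF label in Table 1 |
| Steps per day | device count | none |

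**4. Size of the shift.** In a linear model,

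adjusted difference = overall difference − a × b,

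where a is the group difference in mean SRS (SD units) and b is the within-group standardized slope of outcome on SRS. The article gives neither, so both are assumed. With an overall difference of 0.50 SD:

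| a | b | a × b | Adjusted difference | Share of 0.50 |
|---|---|---|---|---|
| 0 | any | 0 | 0.50 | 0% |
| 0.2 | 0.2 | 0.04 | 0.46 | 8% |
| 0.35 | 0.35 | 0.1225 | 0.378 | 24.5% |
| 0.5 | 0.5 | 0.25 | 0.25 | 50% |
| −0.2 | 0.2 | −0.04 | 0.54 | 8% larger |
| −0.5 | 0.5 | −0.25 | 0.75 | 50% larger |

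**5. Check by simulation.** Group sizes were 34 and 119, the enrolled non-Hispanic White count and the Black plus Hispanic count (79 + 40), with 4,000 replicates.

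- a = b = 0.35: mean unadjusted difference 0.499, SRS-adjusted 0.377
- a = b = 0.5: mean unadjusted difference 0.494, SRS-adjusted 0.246

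This confirms the formula. It is not evidence about the true values of a and b in this sample.

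**The case against.** The covariate sentence is illustrative and conditional. It does not say that the SRS enters every model or that the SRS-adjusted figure is the headline. A reader might infer that the disparity will be reported only after severity adjustment, but the wording does not fix that. An article may also leave the final covariate set to a fuller plan. This stands, and it is why the point is not a stated error.

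A reader might also infer that the SRS is a consequence of inequity, so that adjusting for it is simply wrong. The document does not support that. The Background mentions late diagnosis and unequal care but does not say that these change SRS scores. Table 1 treats the SRS as fairly stable, which favours its use as a background variable, and everyone in the sample is diagnosed and registered, so a selection role is equally plausible. This also stands. Against it, the SRS section concedes some variability and an unknown date, so the pathway role cannot be excluded either.

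A shared ICF label is not shared content, so the overlap argument does not extend to physical function or step counts. The percentages above are arithmetic on assumed inputs.

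What remains is narrow. The only reason given for including severity is confounding, that reason points towards including it, and no contrast without it is named.

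**Conclusion.** The point holds in a limited form. An SRS-adjusted group difference is the difference at equal autism severity. It need not equal the overall difference that Aim 2 describes, and it can be smaller or larger. The shift is zero if mean SRS is equal across groups, and 0.04 to 0.25 SD in either direction if the SRS difference and the slope are each 0.2 to 0.5 in absolute value. That is 8% to 50% of an assumed 0.5 SD effect. These inputs are assumptions, because the article reports no SRS data by group.

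It would go too far to conclude that adjustment will hide a disparity, or that half of one will be lost. The case is clearest for quality of life and instrumental support. For physical function and steps per day, only the question of what the adjusted estimate means applies, not the overlap. The study describes itself as hypothesis-generating, so this is a cheap improvement rather than a proven error.

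**What to change.** For each Aim 2 outcome, report two contrasts with 95% CIs:

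1. adjusted only for demographic covariates such as sex, named as the overall disparity;
2. further adjusted for the SRS, labelled as the difference at equal autism severity.

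Fit both to the same participants, because the Missing Data section expects that some registry variables may be unavailable and a change of sample would blur the comparison. Keep the confounding rationale for the demographic covariates. For severity, say instead that the second model shows how far the difference persists at equal severity. State in advance that the first contrast is the headline.

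This gives the reader the overall difference whichever role severity plays. No new data are needed, since SRS data are an inclusion requirement. The cost is one extra ANCOVA and one extra column per outcome, plus a wording change.

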#### Aim 3: Associations of Physical Function, PA, Personal and Environmental Factors, and QoL, and Moderation by Race and Ethnicity

To examine the associations among physical function, PA, personal and environmental factors, and QoL, multiple linear regression analyses will be performed with QoL as the dependent variable. The primary independent variables will include PROMIS-PF and habitual PA (steps per day), with additional personal and environmental factors entered as indicated by the conceptual model. Covariates such as sex and autism severity will be included as appropriate. We hypothesize that better physical function and greater PA will be associated with better QoL. To evaluate moderation by race and ethnicity, interaction terms between race/ethnicity and physical function, as well as between race/ethnicity and PA, will be entered into the regression models. Continuous predictors will be centered prior to the creation of interaction terms to improve interpretability and reduce multicollinearity. When significant interactions are identified, simple slopes or stratified analyses will be used to further characterize the nature of the moderation effect. Model results will be reported using unstandardized and standardized regression coefficients, 95% CIs, *P* values, and model fit statistics (eg, adjusted *R*^2^). The same a priori power analysis described above applies to aim 3; although this pilot study may be underpowered to detect small effects, it is expected to provide preliminary effect size estimates to guide future research [63].

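### If more than two groups are analysed, pairwise contrasts wait for a significant omnibus test, and group-specific slopes wait for a significant interaction, although the pilot's stated purpose is estimation

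*Protocol article*

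**What the plan says.** All passages are in the protocol article, Statistical Data Analysis Plan.

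- **General rule.** "All analyses will be conducted using 2-sided tests with a significance level of α=.05".
- **Aim 2, main analysis.** An ANCOVA compares adjusted means between non-Hispanic White participants and all minoritized participants combined. No significance condition is attached, and effect sizes with 95% CIs are to accompany the P values.
- **Aim 2, optional expansion.** If more than two racial and ethnic groups are analysed, an omnibus model comes first, and then multiplicity-adjusted "pairwise comparisons where the overall test is statistically significant".
- **Aim 2, purpose.** The sample is expected to suffice for medium-sized effects and "to generate preliminary disparity estimates for future studies".
- **Aim 3, model.** Interactions of race/ethnicity with physical function and with physical activity enter the regression. Model coefficients and 95% CIs are reported without condition.
- **Aim 3, follow-up.** "When significant interactions are identified, simple slopes or stratified analyses will be used to further characterize the nature of the moderation effect".
- **Aim 3, purpose.** The study may be underpowered for small effects, but "it is expected to provide preliminary effect size estimates to guide future research".

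Elsewhere, the Recruitment section under Methods sets separate quotas of 50 Black/African American and 50 Hispanic/Latino participants. The Recruitment section under Results gives the enrolled groups: 79 Black/African American, 40 Hispanic, 34 non-Hispanic White, 1 Asian and 1 not reported.

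**The concern.** A pilot that exists to supply estimates, and that says it may lack power for subgroup and moderation analyses, should not let a significance test decide which group estimates appear. An estimate shown only after passing a low-power test is biased away from zero. If the test is not passed, the estimate is not shown at all.

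The estimates affected are the Black-White, Hispanic-White and Black-Hispanic differences and the slopes within each group. Because recruitment set quotas for two minority groups separately, the three-group analysis is a foreseeable use of the data. The combined contrast does not replace it. That contrast mixes Black and Hispanic participants about 2:1 (79:40), a ratio produced by recruitment, and it would hide differences that run in opposite directions. A later study sized on a filtered pairwise difference would be too small.

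**Working it through.** **1. The plan's own figure.** Under Aim 1: "Assuming a 2-tailed α=.05 and power=0.80, a total sample size of N=155 provides adequate power" for correlations of 0.25 to 0.30 or more. By Fisher's z, power = Φ(atanh(r)·√(N−3) − 1.96).
- r = 0.25: Φ(0.2554 × 12.33 − 1.96) = Φ(1.19) = 88%.
- r = 0.30: Φ(0.3095 × 12.33 − 1.96) = Φ(1.86) = 97%.

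The statement is reproduced. It concerns correlations in the full sample, so it says nothing about contrasts between groups of 34, 79 and 40.

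**2. The ungated Aim 2 contrast.** For 34 against 119 (Black and Hispanic combined), in SD units, the 95% CI half-width is 1.96·√(1/34 + 1/119) = 0.38. Power at d = 0.5 is 72% (noncentral t). This estimate appears whatever its P value, so it is neither missing nor selected.

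**3. The gated pairwise contrasts.** Inputs from the document: two-sided α = 0.05 and groups of 34/79/40. Reviewer's assumptions: SD 1, no covariates, no missing data, and White differing from both other groups by d = 0.2, 0.3 or 0.5. The document gives no numerical effect size for Aim 2.

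The omnibus F has 2 and 150 degrees of freedom and noncentrality λ = d² × 34 × 119/153 = 26.44·d². The chance of passing the gate is the power of this F test. The mean estimate given a significant F comes from 200,000 simulated studies.

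| True d | λ | Gate passed | Contrasts absent | Mean Black-White d if shown | Inflation |
|---|---|---|---|---|---|
| 0.2 | 1.06 | 14% | 86% | 0.463 | 0.463/0.2 = 2.3 |
| 0.3 | 2.38 | 26% | 74% | 0.526 | 0.526/0.3 = 1.75 |
| 0.5 | 6.61 | 62% | 38% | 0.618 | 0.618/0.5 = 1.2 |

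Hispanic-White values are almost the same (0.466, 0.527, 0.619). Over all simulated studies, without the gate, the mean estimates match the true values to within 0.003.

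A less symmetric pattern gives a similar picture. With true White-Black and White-Hispanic differences of 0.3 and 0.2, the gate is passed in 24% of studies, and the mean estimates shown are 0.547 and 0.366.

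**4. Effect on a later study.** Required sample size varies as 1/d². A study sized on the filtered mean would have this fraction of the sample it needs:
- true d = 0.2: (0.2/0.463)² = 0.19
- true d = 0.3: (0.3/0.526)² = 0.33
- true d = 0.5: (0.5/0.618)² = 0.65

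**5. The gated slopes.** Take a two-group moderator (34 against 119) with predictor SD 1 and residual variance 0.75, all assumed. The SE of the slope difference is √0.75 × √(1/34 + 1/119) = 0.168. For true slope differences of 0.2, 0.3 and 0.5, the interaction is significant in 22%, 43% and 84% of studies. The slope follow-up would therefore be absent in about 78%, 57% and 16%. The interaction coefficient is reported in every case.

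**6. Precision if everything is reported.** Unadjusted 95% CI half-widths, 1.96·√(1/n₁ + 1/n₂), in SD units:
- White-Black: 0.40
- White-Hispanic: 0.46
- Black-Hispanic: 0.38

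**The case against.** The strongest reply is that the plan's committed estimates are not filtered at all. The two-group ANCOVA always yields a disparity estimate, and the interaction coefficients always appear with CIs. That is correct. A reader might infer that the pilot could end with no disparity estimate, or that the reported moderation effect is inflated. The document supports neither.

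The Aim 2 gate also sits inside an optional expansion, and quotas are a recruitment rule, not an estimand. This limits the point to that expansion, but the rule for it is already written.

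The gate may be meant only for testing, since effect sizes and CIs are promised without condition and a three-group model also gives adjusted means. That reading is possible. But a comparison that is not run has no P value for an interval to accompany, and an omnibus effect size has neither direction nor group. In Aim 3, point slopes can be derived from the coefficients. A CI for a non-reference group's slope also needs the coefficient covariance.

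The size depends on assumed effects. Aim 2 claims power for medium effects, and at d = 0.5 the inflation is only about 1.2. That stands; even then the contrasts would be absent in about 38% of studies.

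Finally, testing an omnibus first and probing slopes after a significant interaction are conventional, and table layout is often left to an SAP. But here the article itself states the condition, and it works against the article's own purpose.

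**Conclusion.** The point holds in a limited form. The main White-versus-minoritized contrast and the interaction coefficients are safe. The pairwise contrasts in a three-group Aim 2 analysis, and the group-specific slopes in Aim 3, are made conditional on significance, which conflicts with the purpose of providing preliminary estimates.

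At the enrolled sizes, the pairwise contrasts would be missing in about 86%, 74% and 38% of studies at true differences of 0.2, 0.3 and 0.5 SD. When shown, the contrasts with White would be about 2.3, 1.75 and 1.2 times too large. These figures assume that both groups differ equally from White, SD 1, no covariates, and all 153 participants in the three groups analysed. Losses to the step-count wear rules would lower the chance of passing the gate. This is a cheap improvement to reporting and does not put the main Aim 2 or Aim 3 analyses in doubt.

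**What to change.** - **Aim 2.** In any analysis with more than two groups, report the Black-White, Hispanic-White and Black-Hispanic adjusted mean differences with 95% CIs for every outcome, whatever the omnibus P value.
- **Aim 3.** Report each group's slope for physical function and for physical activity with a 95% CI, taken from the joint interaction model, whatever the interaction P value.
- **Both.** Use the omnibus and interaction tests only to decide how claims are worded, not which estimates are shown.

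Analysis is projected to finish in July 2026, and the Missing Data section already provides for documenting and justifying deviations from the analytic plan, so the change can be recorded there.

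The cost is a few more table rows and some wording. The downside is wide intervals: unadjusted half-widths of about 0.4 to 0.5 SD for the pairwise differences, wider still with a multiplicity adjustment. A planner needs to see that imprecision.
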